## Ineligible and Non-Recruited Participants

Participants who are not eligible or decline consent will be thanked for their involvement and interest in the study, and will be asked for consent to be contacted again should eligibility criteria change. Participants can opt to complete a 3 month washout if applicable prior to enrolling.

## Randomisation Procedures

### Randomisation

Women will be randomised in a 1:1 ratio to receive either acupuncture + lifestyle, AEA + lifestyle, or lifestyle alone. Randomisation will be performed in permuted blocks of six.

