# Study Population

## Number of Participants

We aim to analyse 30 participants by the end of treatment. Allowing for a 25% dropout rate which has been reported in similar studies, we will randomise 39 women (13 to real acupuncture, 13 to AEA and 13 to lifestyle alone).

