#### Sequence generation

The randomisation sequence will be created using a computer program by a researcher external to the research team. This researcher will hold the randomisation sequence and will create a series of 39 consecutively numbered sealed opaque envelopes that will contain the ID number and allocation.

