#### Implementation

Once the participant has had eligibility confirmed and has provided written informed consent, she is enrolled and given the next consecutive randomisation ID number, and the research assistant will open the numbered envelope to reveal the allocation. Before opening the envelope the research assistant writes the participant's name on the envelope, the date, and signs the envelope as a record of randomisation. The research assistant will inform the treating acupuncturist of the new enrolment and book the participant’s first appointment.

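### A single published block size of six, with the research assistant opening every envelope in an open-label trial, leaves some allocations deducible in advance; 39 is also not a whole number of blocks

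*Protocol*

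**What the plan says.** The Protocol's Randomisation section (5.5.1) fixes equal allocation to three arms, "Women will be randomised in a 1:1 ratio to receive either acupuncture + lifestyle, AEA + lifestyle, or lifestyle alone", and one block size: "Randomisation will be performed in permuted blocks of six". Under Sequence generation, a researcher outside the team makes and holds the list and "create a series of 39 consecutively numbered sealed opaque envelopes". Under Allocation concealment and Implementation, the research assistant takes the next envelope, writes the participant's name and the date on it and signs it. Then, after eligibility and written consent, "the research assistant will open the numbered envelope to reveal the allocation".

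Section 3 describes the trial as open-label, and the Synopsis lists one centre. No stratification is described, so there is one running sequence. Sections 5.2 and 5.3 allow the research assistant to screen by telephone, contact undecided women within a week, arrange the baseline visit and take written consent. A named investigator may take consent instead, and that investigator also confirms the diagnosis and tells women their eligibility.

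Section 4.1 gives the numbers: "We aim to analyse 30 participants by the end of treatment", and "we will randomise 39 women (13 to real acupuncture, 13 to AEA and 13 to lifestyle alone". Section 5.5.2 says that withdrawn participants are not replaced.

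Nothing in the protocol varies the block size, keeps it from recruiting staff, or provides for a short final block.

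**The concern.** Concealment means that whoever brings a woman to enrolment cannot know or guess the next allocation. An opaque envelope hides its own contents. It does not hide what earlier envelopes imply when the block size is fixed and known. The person who opens every envelope holds the full allocation history, and the block size is printed in the protocol without restriction.

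If the next arm can be anticipated, the timing of a baseline visit, or the warmth of encouragement to an undecided woman, can come to depend on it. The estimates exposed are the between-group differences in weight and BMI (section 2.1.2), which are meant to inform a fully powered trial. The planned ANCOVA (section 9.2) adjusts for the baseline score but not for unmeasured motivation. With about 10 women analysed per arm, a few steered enrolments could move the estimate.

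Separately, the block size, the number of envelopes and the stated arm sizes do not fit together exactly. The block size is fixed in the protocol text itself, so this is not something left to a statistical analysis plan.

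**Working it through.** **Inputs.** Block size 6, three equal arms, so 2 + 2 + 2 per block (section 5.5.1); 39 envelopes (Sequence generation); 13 per arm, 30 to be analysed, 25% dropout (section 4.1); 20-25% attrition (section 9.1).

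**The plan's own total.** 30 / (1 − 0.25) = 40 and 30 / (1 − 0.20) = 37.5, rounded up to 38. The stated 39 lies between these and implies attrition of 1 − 30/39 = 23.1%. The total is therefore consistent with the plan, and 39 = 3 × 13.

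**Predictability within a block.** There are 6!/(2!·2!·2!) = 90 equally likely orderings. Assume an observer who knows the block size and all earlier allocations.

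| Position | Next allocation certain | At least one arm ruled out | Best guess correct |
|---|---|---|---|
| 1 | 0 | 0 | 1/3 |
| 2 | 0 | 0 | 2/5 |
| 3 | 0 | 1/5 | 1/2 |
| 4 | 0 | 3/5 | 8/15 |
| 5 | 1/5 | 1 | 3/5 |
| 6 | 1 | 1 | 1 |
| Sum | 6/5 | 14/5 | 101/30 |

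For example, position 5 is certain when the last two places belong to the same arm: 3 × (2/6 × 1/5) = 1/5. Position 6 is always certain.

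**Over 39 envelopes.** 39/6 = 6.5, so there are six full blocks and then positions 1 to 3 of a seventh.

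- Certain: 6 × 6/5 + 0 = 7.2, and 7.2/39 = 18.5%.
- At least one arm ruled out: 6 × 14/5 + 1/5 = 17.0, and 17/39 = 43.6%.
- Best guess correct: 6 × 101/30 + (1/3 + 2/5 + 1/2) = 20.2 + 1.23 = 21.43, and 21.43/39 = 55.0%. Chance alone gives 13/39 = 33.3%.

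**Balance at 39.** Six full blocks give 12/12/12. The next three envelopes are one per arm with probability 1 × 4/5 × 2/4 = 0.40. So 13/13/13 occurs in 40% of lists and 14/13/12, in some order, in 60%.

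**Effect of the fix.** Blocks of 9+9+6+6+6+3 sum to 39 and give 3+3+2+2+2+1 = 13 per arm in every list. Lists with these blocks in random order were simulated against an observer who knows the mix but not the order. About 2.6 to 2.7 of 39 allocations are certain (roughly 7%, down from 18.5%), and at least one arm is ruled out for about 6.6 of 39 (17%, down from 43.6%). Best-guess accuracy stays at about 55%.

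**The case against.** The strongest reply is that the protocol limits both what the research assistant controls and what she could do with a guess.

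- Screening can be self-administered online. A named investigator confirms each diagnosis and tells women their OGTT result and eligibility, and may take written consent (sections 5.2 and 5.3).
- Before the envelope is opened, a woman has had the glucose tolerance test, worn an accelerometer for 5-7 days and given written consent, and the envelope has been named, dated and signed.
- The primary endpoints are feasibility measures reported descriptively, and the weight comparison is secondary with about 10 women per arm.
- ANCOVA does not need equal arms, and at full enrolment the worst split is 14/13/12.

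Much of this stands. It narrows the route to the timing and encouragement of women who are undecided or already in run-in. It makes the balance point minor, and it makes the percentages upper bounds on what can be predicted. It does not remove the deduction, because none of these steps hides past allocations from the person who opens the envelopes.

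A reader might also infer that the conversion rates among the primary endpoints are biased between arms. The documents do not support that. Section 8 defines conversion as enrolments over enquiries and over potentially eligible women, both pooled ratios measured before allocation with no comparison of arms. Nor do they support reading the research assistant as the sole screener and consenter, or reading most allocations as known in advance.

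**Conclusion.** The point holds as a risk of selection bias in the secondary weight and BMI estimates, through a block size that is both fixed and disclosed. The 18%, 44% and 55% figures assume that the research assistant knows the block size, keeps track of every allocation and works out the consequences. They measure predictability. They do not measure bias, and nothing in the protocol allows an effect on weight to be calculated. The sixth allocation of every full block is deducible under those assumptions, so at least six allocations always are.

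The mismatch between 39 envelopes, blocks of six and 13 per arm is real but small: one arm gains a woman and another loses one in 60% of lists. For a feasibility study with descriptive primary endpoints, that alone would not justify a change.

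Taken together, this is a cheap improvement and not a flaw that undermines the trial.

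**What to change.** Have the external researcher generate the list from randomly ordered blocks of varying size, all multiples of three and totalling 39, for example 9+9+6+6+6+3. At full enrolment this gives exactly 13 per arm. In the protocol, say only that permuted blocks of varying size are used, and record the sizes and mix in a document withheld from recruiting staff. Withholding is the essential part, since varying the sizes alone leaves best-guess accuracy near 55% for someone who knows the mix. The ratio for three arms should also read 1:1:1.

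The cost is one re-run of the list and a new set of envelopes. There are two small downsides. A block of nine can put two arms 3 apart part-way through, against 2 for a block of six, so balance is slightly looser if recruitment stops early. If enrolment has begun, the remaining list must be rebuilt around the allocations already made, or 13 per arm is no longer guaranteed.

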#### Sequence generation

The randomisation sequence will be created using a computer program by a researcher external to the research team. This researcher will hold the randomisation sequence and will create a series of 39 consecutively numbered sealed opaque envelopes that will contain the ID number and allocation.

#### Allocation concealment

The research assistant will allocate participants by selecting the next consecutively number sealed opaque envelope that contains the allocation.

#### Implementation

Once the participant has had eligibility confirmed and has provided written informed consent, she is enrolled and given the next consecutive randomisation ID number, and the research assistant will open the numbered envelope to reveal the allocation. Before opening the envelope the research assistant writes the participant's name on the envelope, the date, and signs the envelope as a record of randomisation. The research assistant will inform the treating acupuncturist of the new enrolment and book the participant’s first appointment.

#### Blinding

Investigators (outcome assessors and investigators involved in statistical analysis) are blinded to treatment allocation but treating acupuncturists and participants are not.

### Withdrawal procedures

Participants are free to withdraw at any time during the study. If they wish to withdraw they can notify either their acupuncturist or the research assistant or [name]. The acupuncturist is to then report the withdrawal to [name]. The research assistant or [name] will call the participant to thank them for their involvement and enquire about the reason for wishing to withdraw although if the participant does not wish to provide a reason or have any further contact with the research team, the research team will respect this wish. If the participant is open to this, the RA or [name] will discuss methods that will assist the participant to continue on with the trial (for example, changing acupuncturist location if this is more convenient). If the participant does not wish to discuss this, it will not be pursued. The participant will be asked if she would be willing to attend for the post-intervention clinic visit or complete the post-intervention surveys. Participants will not be replaced once they are withdrawn.

Data for the withdrawn participant will be used in the analysis unless the participant requests for it to be also withdrawn.

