### Secondary Objectives

2) Determine an effect size for acupuncture and lifestyle vs lifestyle alone and examine for a trend between groups for change in body weight and BMI.

3) Explore the impact of body electro-acupuncture and auricular electro-acupuncture on sympathetic tone and insulin resistance

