# Study Assessments

## Study Assessments

### Study Procedures

Participants will attend for two clinic visits, Baseline/Pre-intervention and Post-intervention.

During these visits they will complete the majority of the outcome measures for the trial.

In addition, the following outcomes are also collected outside of the two clinic visits:

- Credibility of the treatment, expectations, and perceived treatment allocation are collected immediately after the first acupuncture treatment
- Reproductive: Menstrual cyclicity from menstrual diaries
- Participants will complete an exit survey about the acceptability of the study procedures
- Participants will wear an accelerometer for 5-7 days in the week before attending for the baseline visit, and in Week 11
- Participants and treating acupuncturists will collect data on adverse events throughout the study

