## Anthropometric measures and blood pressure

We will measure weight on a calibrated digital scale, waist and hip circumference at the baseline and follow-up clinic visits. We will measure height by stadiometer at the baseline clinic visit. Blood pressure is measured while sitting quietly and after resting quietly for a few minutes, and with both feet on the ground, using an Omron digital automatic standard blood pressure monitor. A large cuff is used if required. Blood pressure on both arms will be obtained initially and the higher blood pressure of the two will be used. Three measurements will be taken, and the average of the last two measurements is recorded. If there is >10mm/Hg or >6mm/Hg difference in systolic or diastolic blood pressure respectively, the participant is asked to rest quietly for five minutes and blood pressure measurement is repeated ([48](#_ENREF_48)).

Anthropometric measures and blood pressure will be measured according to standard procedures as outlined in http://www.cdc.gov/NCHS/data/nhanes/nhanes_07_08/manual_an.pdf

Data will be entered by the Research assistant into the Redcap database.

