## Other outcomes collected during clinic visits

The following data will be collected during clinic visits. Participants may use an online survey or paper surveys. Data on paper surveys will then be manually entered into Redcap by the Research assistant.

- Health related quality of life – the Modified PCOS Questionnaire
- Global quality of life - EQ-5D
- Psychological Symptoms – the DASS 21
- Weight self efficacy – the Weight Efficacy Lifestyle Questionnaire short form
- Internal locus of control – the Internal Health Locus of Control questionnaire
- Demographic questionnaire – see Appendix

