## Proposed Analyses

Recruitment, retention and adherence rates are presented with descriptive statistics. Mixed model ANOVAs will be used to determine within-group differences for continuous outcomes between baseline and 3 months, and ANCOVAs for between-group differences for continuous outcomes with baseline score as a co-variate. Intention-to-treat analysis will be used.

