# Appendix 1 - Schedule of Observations and Procedures

| **Visit/Timepoint** | **Screening (self screening or telephone)** | **Week -1**  **(Run-in)** | **Visit 1**  **Baseline (Allocation)** | **1^st^ acupuncture treatment** | **Visit 2**  **Post intervention** |
| --- | --- | --- | --- | --- | --- |
| Week(s): | **-4 to -2** | **-1** | **0** | **1** | **12** |
| **ENROLMENT** |  |  |  |  |  |
| Eligibility screen | **X** |  |  |  |  |
| Informed Consent |  |  | **X** |  |  |
| 2hr OGTT and Insulin, free and total testosterone, SHBG, Free androgen index |  | **x** |  |  | **x** |
| Physical activity levels |  | **x** |  |  | **X (Week 11)** |
| Allocation |  |  | **X** |  |  |
| **INTERVENTIONS** |  |  |  |  |  |
| Body acupuncture + lifestyle |  |  |  |  |  |
| Auricular electro acupuncture + lifestyle |  |  |  |  |  |
| Lifestyle alone |  |  |  |  |  |
| **ASSESSMENTS** |  |  |  |  |  |
| Credibility and Expectancy Questionnaire |  |  |  | **X** |  |
| Demographic and medical questionnaire |  |  | **X** |  |  |
| Anthropometric measures and blood pressure |  |  | **X** |  | **X** |
| Concomitant Medications |  |  | **X** |  | **X** |
| Surveys – QoL, psychological, weight self efficacy, locus of control |  |  | **X** |  | **X** |
| Heart rate variability by ECG monitor |  |  | **x** |  | **x** |
| Ferriman-Gallwey score |  |  | **X** |  | **X** |
| Exit survey on acceptability of the intervention |  |  |  |  | **X** |
| Adverse Events |  |  | **X** | **X** | **X** |

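### The survey-only option for women who withdraw yields no follow-up weight; a brief weight-only attendance could be named as a middle step

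*Protocol*

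**What the plan says.** On withdrawal, section 5.5.2 of the protocol provides: "The participant will be asked if she would be willing to attend for the post-intervention clinic visit or complete the post-intervention surveys". The same section keeps a withdrawn woman's data in the analysis unless she asks for its removal, rules out replacement, and respects a wish for no further contact.

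On weight, section 8.1 states: "We will measure weight on a calibrated digital scale, waist and hip circumference at the baseline and follow-up clinic visits". Section 7.1.1 fixes the number of visits: "Participants will attend for two clinic visits, Baseline/Pre-intervention and Post-intervention". In the Appendix 1 schedule, anthropometry has its own row, separate from the surveys, which are described as "QoL, psychological, weight self efficacy, locus of control". The section on other outcomes collected during clinic visits lists the instruments. The only one that mentions weight is "the Weight Efficacy Lifestyle Questionnaire short form", a self-efficacy scale.

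On use of the data, the secondary objective (section 2.1.2) is to determine an effect size and to "examine for a trend between groups for change in body weight and BMI". Section 9.2 plans "ANCOVAs for between-group differences for continuous outcomes with baseline score as a co-variate" under intention-to-treat. On numbers, section 4.1 begins "Allowing for a 25% dropout rate which has been reported in similar studies" and arrives at 39 women randomised, 13 per arm, so as to analyse 30.

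**The concern.** The plan does the important thing: it seeks outcomes after withdrawal and keeps them. But of the two options it names, only one returns the outcome on which the effect size is based. A woman who will not attend the post-intervention visit is offered the surveys, and these yield no weight. With only two visits there is no interim weight to fall back on. The coaching service is described as supplying compliance and dietary-habit data, not weight.

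An ANCOVA on follow-up weight needs a follow-up weight. A statistical analysis plan could model the missing values but could not restore a measurement that was never taken. The stakes are some precision and, if women who leave a weight-loss trial differ in weight change from those who stay, some bias in the figure carried to the larger trial.

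**Working it through.** **Reproducing the sample size.** Inputs are 30 analysed and 20–25% attrition (sections 4.1 and 9.1).
- Formula: N = 30 / (1 − d).
- At 20%: 30 / 0.80 = 37.5, so 38. At 25%: 30 / 0.75 = 40.
- The stated 39 lies between the two. It implies a loss of 9 / 39 = 23.1%, or 3 of 13 per arm.

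**What each option returns.**
- Post-intervention clinic visit: weight and waist are measured. Height is taken at baseline only, so follow-up weight is enough for BMI.
- Surveys: quality of life, DASS 21, weight self-efficacy and locus of control. No body weight.

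**Precision.** The half-width of a 95% interval for a pairwise adjusted difference, in residual SD units, with three arms of n and one baseline covariate, is t(0.975, 3n − 4) × √(2/n).

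| Women per arm with follow-up weight | Share of 39 | √(2/n) | Half-width (SD) |
|---|---|---|---|
| 10 | 76.9% | 0.447 | 0.92 |
| 11 | 84.6% | 0.426 | 0.87 |
| 12 | 92.3% | 0.408 | 0.83 |
| 13 | 100% | 0.392 | 0.80 |

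Using two-arm degrees of freedom (2n − 2) instead gives 0.94, 0.89, 0.85 and 0.81, which is the same picture. The rows for 11 to 13 are a range, because the protocol gives no figure for how many withdrawing women would accept a short attendance.

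**Selective loss.** If an arm has 10 completers with mean C and 3 lost women with mean L, the completers' mean differs from the full-arm mean by C − (10C + 3L)/13 = (3/13)(C − L).
- A gap of 1 kg (assumption) gives 0.23 kg; a gap of 2 kg gives 0.46 kg.
- With one of the three recovered, and typical of the lost, the multiplier becomes 10/11 − 10/13 = 0.14, leaving 0.14 to 0.28 kg.
- With the same loss and the same gap in both arms of a comparison, the two shifts cancel in the difference.

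**Scale.** The smallest weight effect in the protocol's background is 1.58 kg, for acupuncture against sham outside PCOS. The shift of 0.23 to 0.46 kg is 15–29% of that. If the residual SD is 2 to 5 kg (assumption), the half-width at 10 per arm is 0.92 × 2 to 0.92 × 5, or about 1.8 to 4.6 kg, and the shift is about 5–25% of it.

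**The case against.** The strongest reply is that section 5.5.2 is permissive. It names the clinic visit first, does not say that every procedure must be completed, and does not stop a woman from attending, being weighed and declining the ECG. A reader might infer that she must accept the whole visit, including a 2-hour glucose tolerance test, or that she is steered to the surveys. The text supports neither. The glucose test is done at a separate pathology collection centre, and section 5.5.2 asks only about the clinic visit. This part of the objection stands. What remains is that a weight-only attendance is not offered, so whether a given woman hears of it depends on who makes the call.

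A reader might also infer that nine weights are lost under the present wording and would be regained under a better one. The protocol does not show this. Nine is the allowance for women not analysed and may already be net of withdrawers who accept the visit. Some will want no contact or will ask for their data to be removed, and a short attendance still means the same trip to Campbelltown. The precision figures are therefore an upper bound.

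Finally, weight is a secondary outcome, the estimate is imprecise even at 13 per arm, and one more request to a woman who has withdrawn is a burden. All of this is fair, and it limits the weight of the point.

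**Conclusion.** The point holds as a cheap improvement, at the level of something the sponsor could do. A woman who takes the survey option has no follow-up weight or BMI, although the plan intends to keep withdrawn women's data in an intention-to-treat analysis.

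The greatest possible gain in precision is a half-width of 0.80 instead of 0.92 residual SD, which requires all nine women to be recovered. A likelier gain is smaller and cannot be estimated from the protocol. The 0.23 to 0.46 kg shift rests on an assumed 1 to 2 kg gap confined to one arm; it illustrates the risk and does not predict it.

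It would be wrong to conclude that the trial's main purpose is compromised. The primary endpoints are recruitment, retention, adherence, acceptability, credibility and safety, and this wording does not affect them. Nor does the protocol contradict itself: it keeps whatever data are obtained, but its named fallback does not obtain this item.

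**What to change.** Reword section 5.5.2 as an ordered request:
1. Attend the post-intervention clinic visit.
2. If that is declined, attend briefly for weight and waist only, on the study scale.
3. Complete the surveys in addition to either attendance, with surveys alone accepted only if both are declined.

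Keep the existing rule that a refusal of further contact is respected.

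The cost is a one-sentence amendment and a visit of a few minutes for at most about nine women, with no new staff or procedure. The downsides are some travel, an extra request to women who have withdrawn, and partial records: weight and waist without heart rate variability or glucose and insulin results, which the synopsis also includes in the effect-size objective.
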